### Data collection

#### Measures

##### GSED

###### GSED SF and LF

The creation of the GSED SF and LF is described elsewhere.^10^ Briefly, we constructed an item bank from previously gathered data and compiled cross-sectional and longitudinal data from 31 countries representing over 73 000 anonymised children with 109 079 assessments (using 22 established ECD instruments).^6 13 14^ Using subject matter expert input and statistical modelling,^15^ we developed two measures intended tocapture child development at population-level and/or to evaluate programmatic impacts: a caregiver-reportedmeasure (GSED SF), and a directly adminsitered measure (GSED LF).^10^ The measures are created paper-based and app-based (GSED App) with built-in administration rules and supporting media-files (see below).

The GSED SF includes 139 items representing emerging skills and behaviours within cognitive, motor, language and social-emotional domains. All items are presented as questions to the caregiver, with binary response options (Yes/No and ‘Don’t Know’) that use start rules based on the child’s age, and stop rules based on age and performance. Assessors record caregiver’s responses, regardless of the assessor’s observations. In the Netherlands only, the GSED SF is completed online by caregivers. The GSED SF administration includes sounds, images and short video clips that assist in understanding, interpretating and administering the items.

The GSED LF includes 155 items capturing similar domains to the SF but, observed by the assessor following start and stop rules based on the child’s age and responses. LF items must either be observed incidentally or by eliciting the behaviour or both, depending on the item. Items are organised into three grids (A, B and C) that enable assessors to measure the child’s performance on similar tasks in succession, making the administration easier for both assessors and children. To further facilitate administration, icons are placed next to each item that inform the assessor whether the item is observed, demonstrated to or by the child, listened for or spoken to the child. The GSED LF uses a locally constructed and low cost kit with basic materials that the child interacts with to demonstrate abilities. The kit is created by local teams with detailed guidance from WHO. Responses of all LF items are binary (skill observed/not observed).

The items in both measures are ordered by difficulty reflecting children’s emerging skills. Based on the analyses from the validation, we will select the items to be included in the final GSED SF and LF versions available for use.

###### Psychosocial form (PF)

Unlike the SF and the LF, the GSED PF has been developed to index non-normative developmental patterns that provide a window into early manifestations of children’s mental health challenges, including internalising and externalising behaviour problems and dysregulation (eg, eating and sleeping). Items capturing developmentally normative information about socio-emotional competencies are included in the GSED SF and LF, as the SDG 4.2 includes children’s psychosocial well-being. Because few instruments have been developed to capture psychosocial difficulties for children under 3 years, little existing data are available and the development of the GSED PF is exploratory. The PF initial prototype was created through a review of existing measures of infant and toddler mental health and consensus by subject matter experts. The GSED PF includes 47 items and reflects caregiver perceptions of the behaviours’ frequency, using response options: often; sometimes; never/almost never. Items are divided into two age groups: 0 to <6 and 6 to <36 months.

##### Contextual and demographic measures

In addition to the GSED, the validation study includes measures of children’s growth and nutrition, health, environmental and contextual information (see table 2 for measures and sources). The selection of measures was based on known biological and social determinants of development,^16^ the demonstrated validity of the contextual measures in at least one low/middle-income country, and efficiency for data collection. See online supplemental file S2 for visit schedules (online supplemental tables S2A and S2B).

10.1136/bmjopen-2022-062562.supp2Supplementary data

**Table 2 T2:** Study measures in addition to GSED

Construct	What the measure captures	Measure	Administration mode	Time for administer (min)
Child health and household socioeconomic status (SES)	Eligibility (exclusion criteria) Demographic information Information about acute child health Delivery and perinatal conditions Breast feeding Child’s health history Household socioeconomic status* Caregiver education Maternal health/chronic illness COVID-19 exposure	Eligibility and contextual form (specifically developed for the study)	Caregiver report	35
Anthropometry	Weight at time of assessment Infant length/child height at the time of assessment Child’s mid-upper arm circumference at time of assessment Child’s head circumference at time of assessment	Anthropometry form	Child assessment	15
*Family/home environment*	Home environment (HOME only) Play/stimulation/interactions between the child and other family members in the home (HOME and FCI)	Home observation for measurement of the environment inventory (HOME)^29^ OR family care indicators (FCI)^30^ †	*HOME*: caregiver report & observation *FCI*: caregiver report	*HOME*: 45 *FCI*: 15
	Child neglect/abuse Exposure to violence or conflict	Childhood Psychosocial Adversity Scale (CPAS)^31^ †	Caregiver report	15
	Family resilience	Brief Resilience Scale (BRS)^32^ †	Caregiver report	1
	Family social support	Family Support Scale (FSS)^33^ †	Caregiver report	5
Caregiver health and well-being	Caregiver depressive symptoms	The Patient Health Questionnaire- 9 (PHQ-9)^34^	Caregiver report	5
Child development	Global child development (0–41 months)	Bayley Scales of Infant and Toddler Development (Bayley-III)^35^ OR Griffiths Mental Development Scales^36^ ‡	Direct child assessment	45–60
	Global child development (24–41 months)	Early Childhood Development Index 2030 (ECDI2030)^4^ §	Caregiver report	10

*Socioeconomic information on this form comes from the standard DHS multiple assets index; however, some sites have adapted the socioeconomic status items to better fit their contexts.

†These measures have been minorly adapted for the purpose of the study.

‡In a subsample (n=150).

§In a subsample (all children of 24–41 months within the predictive validity subsamples in three countries).

DHS, Demographic and Health Survey; GSED, Global Scales for Early Development.

In three sites (Côte d’Ivoire, The Netherlands and The People's Republic of China) where administration of the Home Observation for Measurement of the Environment Inventory is not feasible, household stimulation data and caregiver–child activities are collected using Family Care Indicators. In all sites, a concurrent measure of child development (Bayley-III or Griffiths Mental Development Scales) is administered in a subsample of children to determine concurrent validity of GSED to a well-established measure of the same construct.

#### Schedule

Data collection is scheduled over one to three visits depending on the study site to accommodate rules of measure administration order and location. The first administration of the GSED SF and PF is completed at home (or online in the Netherlands) to test it in the setting intended for future use (eg, Multiple Indicator Cluster Surveys or Demographic and Health Surveys) and prior to administration of the GSED LF. The GSED LF is administered in a controlled environment (eg, clinic) to match the required concurrent validity testing protocols. For the concurrent validation, the GSED and concurrent measures are administered in the same location on different days and counter-balanced in order of administration.

#### Training and quality control

Training of local master trainers is performed by the WHO team for the GSED SF, PF and LF, using slide presentations, discussion forums, audio–visual aids and practice exercises. Local master trainers are responsible for training local field teams using materials adapted and translated to local languages. Reliable administration of the GSED measures must be met (inter-rater agreement with a master trainer of ≥90%) for certification.

To ensure quality assurance, 10% of all the study visits are observed by the study supervisor in person (or through video-recording in the Netherlands), covering each child age band and certified assessors. Supervisors independently complete questionnaires being administered by the assessor and complete a fidelity checklist. Assessors are given feedback based on checklist score. Supervisors review quality assurance findings with the WHO biweekly, along with discussions with the subject matter experts for further resolution, as needed.

The GSED application software for data collection has built-in data range and consistency checks. Data managers review and resolve issues daily in consultation with the local field team and/or WHO team.

### Sample size

Sample size determination was based on the primary aim of assessing the psychometric properties of the GSED. To have sufficient power to estimate measurement parameters (abilities and difficulties) needed to calculate the D-score and DAZ scores at baseline and to detect DIF of 1 logit with a power of 1−β=0.90 and a two-sided significance level of α=0.05, a sample of n=1248 per site is required. Given the rapidity of development of children at this age, the latent trait is longer than tends to be found in educational tests which focus on a narrower ability range. The easiest item in our tool ‘Does your child smile?’ has a difficulty of −13.2 logits (1.1 on the D-score scale) and the most difficult item has a difficulty of 8.4 logits (88.86 on the D-Score scale), a 21.6 logit span. Thus, a one logit difference is not particularly large, given the length of the latent trait. This sample size was calculated via optimisation of the sample size at (a) each age/sex stratum and (b) overall on 1000 simulated datasets generated from parameters suggested by the Rasch GSED model. See online supplemental file S1 for additional details.

DAZ scores from the GSED SF and LF will be used to conduct validity analyses to ensure that the measures are capturing the construct they are purported to measure (construct validity). Concurrent validity will be assessed by correlating age-corrected Bayley-III or Griffiths Mental Development Scales scores with GSED DAZ scores. We anticipate that these scores will have low to moderate positive correlations. Convergent validity will be supported by statistically significant positive correlations (with 95% CI) between the GSED scores and continuous contextual measures with prior evidence of association with child development. Comparisons between ‘known groups’ will be made using the following variables: maternal education, home learning opportunities, home environment, socioeconomic status, maternal mental health and child anthropometry, and stunting to determine if scores discriminate between high and low categories for each variable using mean DAZ scores.

GSED scores at baseline and follow-up will be correlated for predictive validity (positive association between baseline and at 6 months) and mixed-effects linear regression used to adjust for other contextual covariates and baseline scores.

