## Aims

The primary aim of this study is to validate the GSED measures,^11^ through testing for measurement invariance and evaluation of the psychometric properties to measure development among children under 3 years (<36 months) globally (including creation of D-scores and Development for Age Z-score (DAZ)).

Specific objectives:

Fit a Rasch model to the item data to calculate the D-scores and DAZ.Investigate differential item functioning (DIF) and differential test functioning (DTF) across sites to determine measurement invariance.Examine psychometric properties of the GSED SF and LF:Test–retest and inter-rater reliability (score and item level).Concurrent validity (association between scores on GSED and Bayley Scales of Infant and Toddler Development (Bayley-III) or Griffiths Scales of Child Development administered concurrently).^12^Convergent validity (strength of association between GSED D-scores and other theoretically relevant constructs).Predictive validity (association between GSED scores 6 months after initial assessment).

The secondary aims are to: (1) establish preliminary reference scores (The population has not been selected as a representative sample of all children aged <3 years in each site (as would happen in a countrywide population census). Selection and recruitment of a representative sample was beyond the scope of this study and not required for validation purposes. We are therefore developing ‘reference scores’ which should not be interpreted as population-sampled norms.) for optimal development on the D-score (GSED SF and LF), (2) develop and validate an adaptive testing algorithm and (3) obtain preliminary validity data on the psychometric properties of the GSED PF.

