#### Sampling frame and schemes

Sample size for recruitment within each site is 1248 children (total 8736 children) across seven countries. After consent is provided, children are allocated by sex and age groups using a randomization procedure to one of several sampling schema (eg, predictive, reference-score, reliability; figure 2). See sampling in online supplemental table S1 for sampling frame. Out of the full site sample of 1248 children, 504 children per site are randomly selected for re-evaluation 6 months later to assess predictive validity (primary aim). A second scheme indicates the minimum subsample of children needed to calculate preliminary reference scores (secondary aim) that will facilitate cross-country comparisons. To maximise precision of parameter estimates, larger quotas are kept for the youngest age brackets where rates of development are accelerated. A third scheme addresses inter-rater reliability for 90 children per site using two assessors who independently assess the same child sequentially or within 24 hours^12^ (We note that this procedure differs from typical inter-rater reliability (IRR) designs which involve simultaneous scoring of a single assessment. This sequential design was necessitated by logistical constraints. Given that this design captures both variance due to differences in raters and differences in occasions, the observed IRR represents a lower bound for the true inter-rater reliability of the assessments.). Test–retest (intra-rater reliability) is performed by inviting 50 children per site to return for repeat assessment with the same rater within 7–10 days. For concurrent validity, to assess the GSED against the Bayley-III, a sample size of n=150 per country produces a two-sided 95% CI 0.15 to 0.44, when the estimate of Pearson’s product-moment correlation is 0.3, with an equal spread of participants tested across age and sex.

10.1136/bmjopen-2022-062562.supp1Supplementary data

In the Netherlands, the GSED SF and PF are administered online. A subset of participants (n=32) are interviewed face-to-face to compare method of administration. To determine test–retest reliability (intra-rater reliability), the primary caregiver completes the SF and PS form online and then a second time 7–10 days later.

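### The convergent-validity criterion asks for 'positive' correlations with every continuous contextual measure, which is the wrong sign for the depression and adversity scales if higher scores mean worse

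*Protocol article*

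**What the plan says.** The Aims list convergent validity among the psychometric properties to be examined under the primary aim and define it by magnitude: "Convergent validity (strength of association between GSED D-scores and other theoretically relevant constructs".

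The Statistical analysis section turns this into a criterion: "Convergent validity will be supported by statistically significant positive correlations (with 95% CI) between the GSED scores and continuous contextual measures". The measures that qualify are described only as "continuous contextual measures with prior evidence of association with child development". The article gives no list of them, no expected sign for each, no note on reverse scoring and no size of correlation. The same paragraph says that DAZ scores are used for the validity analyses. It then adds known-groups comparisons of mean DAZ, with maternal mental health among the grouping variables.

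Table 2, in the section on contextual and demographic measures, includes the PHQ-9, described as capturing "Caregiver depressive symptoms", and the CPAS, described as capturing "Child neglect/abuse Exposure to violence or conflict". It also holds measures for which a positive relation with development is the natural expectation, such as home stimulation, socioeconomic status, family support and resilience.

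On numbers, the article states: "Sample size for recruitment within each site is 1248 children (total 8736 children) across seven countries". In Table 2 only the Bayley-III/Griffiths and the ECDI2030 carry a subsample footnote.

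**The concern.** One sign is prescribed for a set of measures that do not all point the same way. Depressive symptoms in the caregiver, and neglect, abuse or violence around the child, are risks. The article treats them as such: the Psychosocial form section puts family and community violence among the indicators of high psychosocial stress. If a higher score on these scales means more of the risk, a valid developmental score should correlate negatively with them. Read literally, the criterion gives no credit for that result.

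There is also a mismatch between objective and criterion. The Aims ask how strong the association is; the criterion asks whether it is significant and positive. With more than a thousand children per site, a correlation can be significant while remaining weak.

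At stake is how one objective of the primary aim is reported. Evidence in favour of the instrument could be left uncounted, or the sign convention could be settled only after the results are known.

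**Working it through.** **Inputs**
- n = 1248 per site (Sampling frame and schemes). That the PHQ-9 and CPAS are collected in all children is inferred from the lack of a subsample footnote in Table 2.
- Two-sided alpha of 0.05. The Sample size section states it for differential item functioning; it is assumed here for the correlations because no other level is given.
- Scale direction, higher = worse. This is inferred from the constructs; the article does not state it.
- True correlation of -0.10 with a risk scale: an illustrative assumption.

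**1. The plan's own correlation figure.** For concurrent validity the article gives n=150, r=0.3 and a 95% CI of 0.15 to 0.44. The Fisher interval is tanh(atanh(r) ± 1.96/√(n-3)):
- atanh(0.3) = 0.3095 and 1.96/√147 = 0.1617
- tanh(0.1479) = 0.147 and tanh(0.4712) = 0.439

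The stated interval is reproduced, so the same formula is used below.

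**2. Direction.** With n=1248, √1245 = 35.285 and atanh(0.10) = 0.1003, so the mean of the test statistic is -0.1003 × 35.285 = -3.54.
- Probability of a significant negative result: Φ(3.54 - 1.96) = Φ(1.58) = 0.943
- Probability of a significant positive result: Φ(-3.54 - 1.96) = Φ(-5.50), about 2 × 10⁻⁸

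The result that theory predicts occurs about 94% of the time and fails the printed wording whenever it occurs.

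**3. Size.** The smallest observed |r| with two-sided p<0.05 is t/√(n-2+t²), with t the 0.975 quantile on n-2 degrees of freedom.

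| n | smallest significant \|r\| | r² |
|---|---|---|
| 1248 (one site) | 0.0555 | 0.31% |
| 504 (the number per site re-evaluated at 6 months, as a lower-n check) | 0.087 | 0.76% |

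An observed r of 0.06 at n=1248 has a 95% CI of 0.005 to 0.115 and would meet the criterion.

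**4. How often small true correlations pass.** The power is Φ(atanh(r)·√(n-3) - 1.96). At n=1248 this gives:
- true r = 0.03: 18%
- true r = 0.05: 42%
- true r = 0.08: 81%
- true r = 0.10: 94%

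**5. What a fixed floor would do.** For the lower 95% limit to reach 0.10 at n=1248, the observed r must be at least tanh(atanh(0.10) + 1.96/35.285) = 0.155. A true r of 0.15 would achieve this with probability Φ((atanh(0.15) - atanh(0.1546)) × 35.285) = Φ(-0.17), about 43% per site.

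**The case against.** The article does not say which measures enter the convergent correlations, and it gives both scales another use: maternal mental health appears in the known-groups comparisons, and violence in the analyses of the psychosocial form. Orienting scales and tabulating expected signs is routine analysis-plan content, and the full plan is not shown. This stands as a limit. Inclusion is an inference, firmer for the PHQ-9 than for the CPAS, which rests on its place in Table 2. It does not remove the point, because the article states a sign, and states it without qualification.

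A reader might infer that the rule would produce false support from the risk scales. Step 2 shows that this has no practical weight: when the true relation is negative, a significant positive result is almost impossible. The consequence is support left uncounted, and the known-groups comparison would still show the relation with maternal mental health.

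A reader might also infer that the criterion can hardly fail for the remaining measures. Step 4 does not bear this out within a site: a true correlation of 0.03 fails about four times in five, and one of 0.05 more often than not. Nor can the argument lean on all 8736 children. Pooling across sites is not a stated analysis for these correlations, and it could not apply to the HOME inventory, which three sites replace with the Family Care Indicators, leaving at most 4 × 1248 = 4992.

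Finally, the article speaks of support, promises 95% CIs and sets no pass/fail rule for the instrument on this property. Size and precision will therefore be visible, and a numerical floor such as 0.10 is a choice, not something the documents require.

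**Conclusion.** The direction of the criterion is wrong as printed for any contextual measure scored so that higher is worse. On the constructs in Table 2, that means the PHQ-9 and probably the CPAS. At a true correlation of -0.10, the expected significant negative result appears in about 94% of samples of 1248 and would not count as support. This rests on three assumptions: that the scales enter the correlations, that they are not reverse-scored, and that all 1248 children at a site contribute.

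The size part holds in a weaker form. The Aims speak of strength, the criterion speaks of significance, and at n=1248 the two separate from an observed |r| of about 0.055 upwards (two-sided 5% assumed). That is a reason to interpret the estimate and its interval. It does not show that the criterion is empty.

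Severity is minor to moderate. A stated criterion needs correcting, but the article ties neither item selection nor sample size to it.

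**What to change.** 1. In the Statistical analysis section, replace the requirement of a positive correlation with one in the pre-specified expected direction. Add a short table of the continuous contextual measures that enter the analysis, with the expected sign of each: negative for the PHQ-9 and CPAS, or a statement that they are reverse-scored.
2. State that convergent validity is interpreted from the size of r and its 95% CI within each site, in line with the definition in the Aims, and not from significance alone.
3. Optional: a minimum correlation against which the confidence limit is judged. A floor of 0.10 is only an example and has a price: by step 5, a true correlation of 0.15 would meet it in fewer than half of sites.

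Items 1 and 2 cost one small table and two sentences, with no new data and no change in sample size. They should be settled before the correlations are seen, so that neither sign nor size is chosen afterwards.
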